# évaluation CRITERIA

**Main criteria:**

• Quantification of body weight loss and the loss of total body fat
• Variation in the microbiota Firmicutes / Bacteroidetes
• Quantification of the reduction of systemic inflammation (CRP -us , IL6 , TNF , serum amyloid )
• Analysis of profiles of gene function ( gene regulatory networks analyzed by microarray ) interacting with inflammatory functions in the kinetics of weight loss
• Quantification of macrophage infiltration by gene and protein markers (CD11b CD68, and pro markers (CD40) or anti- inflammatory (CD163, mannose receptor)): in the subcutaneous adipose tissue before and after weight loss and linking with the reduction of systemic inflammation (CRP -us, IL6, TNF, serum amyloid).
• Analysis of interactions between the changes of the intestinal flora, biological variations and adaptations (including inflammatory) adipose tissue.

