**Treatment of biological samples**

The serum samples to be assayed for markers of adiposity and inflammatory factors will be analyzed at our Inserm Unit U872 (Eq 7). The serum bank will be stored by the Inserm Unit U872 (Eq 7). The experiments in adipose tissue will be carried out by the Inserm Laboratory U872 (Eq 7) – Research Center in Human Nutrition of Ile de France (Paris 6) who has the necessary equipment for molecular and cellular biology techniques (whole-genome DNA microarray dedicated to inflammation, and real-time quantitative PCR) in collaboration with the functional genomics Inserm network, who develops microarray-specific analysis methods.

1) **Morphology and cellular population**

Adipocyte diameters will be measured for each subject before and after each period.

2) **Gene expression**

The extraction of total ARNs will be done for the freezed tissues using the adapted kit RNasy Mini Kit (QIAGEN, requis, CA) adapté. Due to the small amount of obtained adipose tissue and the difficuklty of rendement, we will use the methode put and validated by the INSER ([name]), who optimized this method in the European network *MolPage*. On the other hand from total adipose tissue we will identify the candidat genes. Associted to the inflammatory markers, the macrophages (CD 68, CD11b, CD163, mannose receptors, CD40), and the adipokines (leptin, adiponectin), that might be associated to the uinflammatory phenomena.

We will identify also the classes of genetic functions that could be associated to these modifications of the inflammation during body weight loss induced by the hypocaloric diet.

We will study the individual kinetics of gene expression by at day 0, day 7, day 28 and day 42 and after the 6 week stabilization period.

**Urine samples collection:** Samples of urine will be also collected at each time point and conserved at – 20°C.

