Results from cDNA microarrays will be analyzed by the Inserm Unit U872 (Team 7), where new strategies of oligonucleotide microarray data analysis are being developed. Experimental results will be stored in the SMD database (http://genome-www5.stanford.edu). We will use a certain number of functions developed for R software (steps of filtering, normalization, selection of differentially expressed genes, groups, etc) in order to highlight groups of modified genes. The translation of gene expression data into the corresponding biological mechanisms (commonly called functional analysis or profiling) is considered a major challenge and is an essential step in the elucidation of the biological phenomena underlying the experimental models being studied. Functional annotation will be used to connect sets of genes in the genome with molecular networks that interact within the cell, in order to illustrate the higher order biological information related to metabolic pathways and their regulation. We will search automatic descriptions of enrichment through the databases Gene Ontology (GO) or KEGG (Kyoto Encyclopedia for Genes and Genomes). Our functional analysis will essentially be centered on inflammatory factors and their associated gene networks. Two algorithms, MAGO and FunCluser, have already been designed with this in mind by our team. They automatically link gene transcription microarray data with the genes’ biological roles in order to investigate significant functional changes in the experiment compared to other functions represented on the chip. We will introduce appropriate statistical analysis to take into account multiple testing (False Discovery rate). A computer engineer in the U872 Inserm team will be dedicated to the work of microarray analysis.

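### Functional change is scored against all functions on the chip, but changed genes are picked only after an undefined filter; the reference should be the genes that were tested

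*Protocol*

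**What the plan says.** In the protocol's section on statistical analysis, under Expression studies, the array data go through R functions covering "steps of filtering, normalization, selection of differentially expressed genes, groups, etc". Enrichment follows: "We will search automatic descriptions of enrichment through the databases Gene Ontology (GO) or KEGG". Two in-house algorithms then link the array results to biological roles in order to "investigate significant functional changes in the experiment compared to other functions represented on the chip". The text names the chip as the comparator and does not limit it to genes that survived the filter. It does not say what the filter removes genes for.

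The emphasis is stated: "Our functional analysis will essentially be centered on inflammatory factors and their associated gene networks". For multiplicity the section promises "appropriate statistical analysis to take into account multiple testing (False Discovery rate)", with no level and no indication whether it applies to genes, functions or both.

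The result matters because the evaluation criteria list, among six main criteria, "Analysis of profiles of gene function ( gene regulatory networks analyzed by microarray ) interacting with inflammatory functions in the kinetics of weight loss".

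**The concern.** An enrichment score asks whether a function has more changed genes than expected if changed genes fell at random across functions. The expectation must be formed over the genes that had a chance of being called changed. If genes are filtered first and the expectation is formed over the whole chip, the score mixes two questions: whether the diet changed the function, and whether the function's genes tend to pass the filter in this tissue.

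Only subcutaneous adipose tissue is assayed. With a filter based on expression, passing rates would plausibly differ between functions. Well-represented functions would then look changed too easily, and poorly represented ones would be harder to detect. For a main criterion centred on inflammatory networks, the error could run in either direction.

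**Working it through.** **Inputs.** The protocol gives no chip size, filter rate, list size or enrichment test, so there is no stated figure to reproduce. All of the following are assumptions:

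- N = 20,000 genes on the chip.
- F = 10,000 genes pass the filter.
- One function has K = 400 genes on the chip, of which k pass.
- D changed genes are drawn at random from the F genes, so there is no effect specific to the function.
- The test is a one-sided hypergeometric test at 0.05.

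**Expected overlap.**

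- Actual expectation: D × k / F.
- Expectation with the chip as reference: D × K / N.
- Ratio of the two: (k/K) ÷ (F/N), the function's passing rate divided by the chip's passing rate. Any ratio other than 1 is bias.

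**Worked case.** Take D = 500 and 70% passing, so k = 280.

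- Actual expectation: 500 × 280 / 10,000 = 14.
- Chip expectation: 500 × 400 / 20,000 = 10.
- Ratio: 0.70 / 0.50 = 1.4.
- Against the chip, 16 overlapping genes are enough for p ≤ 0.05. Against the filtered genes, 21 are needed.
- The true overlap is hypergeometric (10,000; 280; 500), so P(overlap ≥ 16) = 0.327 and P(overlap ≥ 21) = 0.041.

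**False-call rate by length of the changed list (exact):**

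| Changed genes D | Chip reference, 60% / 70% / 80% passing | Filtered reference, range |
| --- | --- | --- |
| 20 | 0.012 / 0.017 / 0.025 | 0.012–0.025 |
| 100 | 0.033 / 0.061 / 0.101 | 0.022–0.041 |
| 500 | 0.147 / 0.327 / 0.537 | 0.031–0.041 |
| 1,000 | 0.219 / 0.530 / 0.801 | 0.036–0.047 |

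**Neutral filter.** If the function passes at the chip rate (50%), the ratio is 1, and the chip reference gives 0.043 with D = 500. There is no inflation.

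**Second set of assumptions.** Take a 20,000-gene chip with 40% passing, a 100-gene function with every gene passing, and 500 changed genes. The expected overlap is 500 × 100 / 8,000 = 6.25, against 500 × 100 / 20,000 = 2.50 by the chip. The false-call rate is 0.601 with the chip reference and 0.047 with the filtered reference. Where functions passed at the overall rate, the chip reference gave 0.004 to 0.049.

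**Loss of power.** Return to N = 20,000, F = 10,000, K = 400 and D = 500, with 30% passing. A function whose genes have twice the odds of being changed is detected 10% of the time with the chip reference and 59% with the filtered one. At three and four times the odds, the chip reference still detects it 55% and 89% of the time.

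**False Discovery Rate.** The procedure takes the p-values as given. If they are computed against the wrong expectation, adjusting them for multiplicity does not restore the error rate.

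**The case against.** The strongest reply is that the defect is inferred. The clause about the chip is a one-line description of two existing algorithms. It compares functions with functions and names no background gene list and no test; the hypergeometric test is an assumption here. The filter is undefined, and a spot-quality filter unrelated to function would do no harm. Filter rules and background sets are also commonly left to an analysis plan. This limits what can be claimed: the whole-chip background is the natural reading, not the only one, and the bias is conditional on the filter. It does not remove the point, because the protocol does not leave the comparator open. It names one, after placing a filter ahead of gene selection.

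The reply is also right about size and consequence. With short lists there is little or no inflation. This is one of six main criteria, no decision rule is tied to an enrichment p-value, and the inflammatory conclusions have separate support from candidate genes, protein markers and circulating markers.

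A reader might infer three stronger things that the document does not support:

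- That functions would be declared changed with no diet effect at all. The calculation needs a list of changed genes. What is absent is an effect specific to the function. If the diet changed no gene and the False Discovery Rate governed gene selection, the list would usually be very short or empty; the protocol does not say whether it applies there.
- That real changes in poorly represented functions would be masked. Power falls, but strong changes are still mostly found.
- That the description of the array as "whole-genome DNA microarray dedicated to inflammation" proves the reference is unstable. It is unclear wording in a roughly translated section, and the point does not depend on it.

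**Conclusion.** The point holds in conditional form. The comparator as worded does not match the set of genes from which changed genes are drawn. If the filter is related to adipose expression, this inflates false calls for functions that pass more often than average and lowers power for those that pass less often.

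The size cannot be derived from the protocol. Under the main assumptions it runs from negligible with 20 changed genes to as much as 80% with 1,000, and it is nil for a filter neutral to function. The large figures need several hundred changed genes. The correction is worth making because it concerns a main criterion and costs almost nothing.

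**What to change.** Under Expression studies, replace the comparison with functions on the chip by a comparison with functions represented among the genes that passed the filter and were tested for differential expression. Count each function's size within that same set, and apply the False Discovery Rate to the resulting p-values. State the filter criterion alongside.

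The cost is about one sentence in the protocol and a different background gene list in the analysis, assuming the in-house software accepts one, which the document does not show. No further samples, arrays or participants are needed. The downside is small: some functions will lose significance, and those with very few tested genes cannot be assessed. With a neutral filter, the change leaves error rates essentially as they were.

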# Communication

The results of this study may be presented at scientific conferences or published in medical journals. Publishing projects and findings will be discussed jointly by the principal investigator of this clinical trial coordinator and project coordinator of the ANR (Micro-Obes) and the promoter, their content and their conclusions before final versions of abstracts, texts or posters are fixed.

This restriction also applies to changes that may subsequently be requested by peer reviewers for conferences and journals. The principal investigator, coordinator and promoter also agree not to publish the data in the study without the prior consent of the other parties. In addition, the support of the sponsor must be mentioned.

# SUBSTANTIAL modifications TO THE PROTOCOl

## Procedure of the sponsor on the establishment of an amendment

Any substantial changes to the protocol will become an application for an amendment addressed to the Inserm sponsor, which will be attached to the amended protocol accordingly.

The CPP must be notified of any amendment to the study protocol if the alterations planned change ethical or medico-scientific aspects of the study (endpoint, extension of the period of inclusion, constraints and risks experienced by participants ...).

The amended protocol may also be a request for authorization from the competent authority of the protocol, namely the Directorate General of Health.

# ConfidentialitY

The investigator will ensure that confidentiality regarding each volunteer study participant is guaranteed.

Access to clinical data and sources will be direct in case of audits commissioned by the sponsor or inspections by the competent administrative authorities.

# QUALITY Assurance

The study is conducted in a university hospital experienced in quality control procedures and expertise of stakeholders.

Quality and quality control will be provided by the clinical research team (CRNH - Ile de France by [name], [name] and [name] (ARC- APHP).
The quality of the test is governed by a strict compliance with all internal procedures of the institution University Hospital ( Pitié Salpêtrière, Paris), by the application of good clinical practice.
Quality control will be carried out internally every two months.
Quality control will be carried out throughout the study, under the responsibility of the principal investigator and coordinator ([name] and [name]).

This quality control will include:
- The data collected during the study
- The consents of all subjects included
- Materials for the investigation

The relevant information will be accessible to the investigator in case of control.

